### Outcomes measures

Patients will be asked to obtain Informed consent. Next to that, everyone’s demographic and anthropometric indices checklist are filled, and a nutritionist will teach general nutritional recommendations. The dietary intake of individuals will be evaluated by the 3-day food registration questionnaire (two week days and one weekend day). Also, before the intervention, patients will be paid to complete their standard questionnaires, including KD-QOL and HADS, to assess the quality of life, depression, and anxiety. If the patient is illiterate, the information will be received by interviewing. At baseline and the end of the 12th week, 10 mL of blood will be obtained from each patient after 12 h of fasting. Blood serum will be stored at refrigerator temperature (− 70 °C).

The primary clinical outcome measures for the trial are renal function tests as creatinine, urea, uric acid, urine volume, indices related to blood glucose including FBS, HbA1c, GA, serum insulin, insulin resistance and β cell function, indices related to oxidative stress, and inflammation including SOD, MDA, TAC, and hs-CRP. Secondary outcomes include KDQOL and HADS questionnaires and the amount of energy and macronutrients intake.

The process for assessing the activity of hs-CRP, MDA, SOD, and TAC will be done by Navand assay kit (Navandsalamat, Iran) according to the company package insert instruction. The serum insulin level, HbA1c, and GA will be measured by the enzyme-linked immunosorbent assay (ELISA) method. Biochemistry Solutions will also measure creatinine, urea, uric acid, and FBS.

To determine insulin resistance and β cell function, HOMA-IR and HOMA-B formula will be used, respectively [22].

HOMA-IR=$$ \frac{\  glucose\left(\frac{mg}{dl}\right)\times insulin}{405} $$ HOMA-B =$$ \frac{fasting\ insulin\times 20}{fasting\ glucose-3.5} $$

The reliability of laboratory methods by sending the first ten samples of experiments with two different names to the laboratory expert and investigating the level of agreement between them will be determined. Also, body composition will be evaluated by the bioelectrical impedance analysis (BIA) method.

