### Sample size

The sample size for this trial was calculated based on the primary outcome using the G-power software [23] (procedure of two independent groups) or formula $$ n=\frac{\left({\sigma}_1^2+{\sigma}_2^2\right){\left({Z}_{\frac{\alpha }{2}}+{Z}_{\beta}\right)}^2}{{\left({\mu}_1-{\mu}_2\right)}^2} $$. According to the previous results of NS on renal failure [1], the percentage reduction in creatinine (the primary outcome) is 32.43% in the NS group and 9.84% in the placebo group. By considering an alpha error of 0.05, and the power of 90%, the minimum sample size required for each group is 20 participants, in which with predicting a 15% loss, it will be 23 patients in each group. In total, 46 participants will be recruited in this trial.

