### Stratified randomization

The patients will be allocated to either a NS oil or control group by block randomization after stratification based on the frequency of hemodialysis per week (2 or 3 times per week) and the amount of blood sugar (FBS < 120 mg/dL, FBS = 120–200 mg/dL and FBS > 200 mg/dL). This process will be carried out by a statistics specialist using RAS (random allocation software) in block sizes of 4.

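### HOMA-B is printed with mmol/L constants and no glucose unit, beside a mg/dL HOMA-IR, in a trial that states glucose only in mg/dL

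*Protocol article*

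**What the plan says.** In the protocol article, Outcomes measures, the two derived glycaemic indices are introduced together: "To determine insulin resistance and β cell function, HOMA-IR and HOMA-B formula will be used, respectively". HOMA-IR carries an explicit glucose unit and the divisor 405: "glucose\left(\frac{mg}{dl}\right)\times insulin}{405". HOMA-B follows on the same line with no unit for glucose: "HOMA-B =$$ \frac{fasting\ insulin\times 20}{fasting\ glucose-3.5". Neither formula gives a unit for insulin.

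The same section counts both indices among the primary outcome measures: "indices related to blood glucose including FBS, HbA1c, GA, serum insulin, insulin resistance and β cell function". β cell function is also part of the first specific objective at the end of the Introduction.

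The only other place that gives a glucose unit is Stratified randomization, where the strata are "FBS < 120 mg/dL, FBS = 120–200 mg/dL and FBS > 200 mg/dL". No mmol/L value and no conversion factor appears in the document.

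**The concern.** The two formulas need glucose in different units, but only one is labelled. An analyst who has just applied the mg/dL label to HOMA-IR, and who holds fasting glucose in mg/dL for the strata, has no instruction to convert before computing HOMA-B.

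The mismatch is visible from the document's own figures. Against the stratum cut-points, an offset of 3.5 is 2.9% of 120 and 1.75% of 200, so subtracting it from a mg/dL value does almost nothing. Read in mmol/L, the same offset equals 63 mg/dL, which is 52.5% of 120 and 31.5% of 200, and it largely determines how the index responds to glucose.

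At stake is a listed primary outcome in a trial of a supplement expected to lower glucose. Glucose is the component through which a unit error would distort a treatment comparison as well as rescale the index.

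**Working it through.** The document states no HOMA-B value, so there is no figure to reproduce. The check is algebra on the printed formulas.

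**Inputs from the protocol article**
- HOMA-IR: glucose (mg/dL) × insulin / 405 (Outcomes measures).
- HOMA-B: 20 × insulin / (glucose − 3.5), glucose unit not given (Outcomes measures).
- Fasting glucose cut-points 120 and 200 mg/dL (Stratified randomization).

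**Assumptions**
- 1 mmol/L of glucose is 18 mg/dL.
- Insulin is in µU/mL, the usual unit for these indices; the document gives none.
- 150 and 300 mg/dL are added for illustration, because the document gives no distribution of fasting glucose.

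**Step 1: which unit does each formula use?** 405 = 22.5 × 18, so HOMA-IR is the mg/dL form. For HOMA-B, with G in mg/dL:

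20 / (G/18 − 3.5) = 20 × 18 / (G − 3.5 × 18) = 360 / (G − 63).

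The constants for mg/dL are therefore 360 and 63. The printed 20 and 3.5 are the mmol/L pair.

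**Step 2: scale error if mg/dL is entered as printed.** Correct value divided by misapplied value:

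[360 / (G − 63)] / [20 / (G − 3.5)] = 18 (G − 3.5) / (G − 63).

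**Step 3: effect on a small glucose-driven relative change, insulin fixed.** The proportional slope of the correct index on glucose is −G/(G − 63); that of the misapplied index is −G/(G − 3.5). The share of the effect that is kept is (G − 63) / (G − 3.5).

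| G (mg/dL) | Correct, per unit insulin | Misapplied, per unit insulin | Correct / misapplied | Share of effect kept |
|---|---|---|---|---|
| 120 | 360/57 = 6.32 | 20/116.5 = 0.172 | 36.8 | 57/116.5 = 0.49 |
| 150 | 360/87 = 4.14 | 20/146.5 = 0.137 | 30.3 | 87/146.5 = 0.59 |
| 200 | 360/137 = 2.63 | 20/196.5 = 0.102 | 25.8 | 137/196.5 = 0.70 |
| 300 | 360/237 = 1.52 | 20/296.5 = 0.067 | 22.5 | 237/296.5 = 0.80 |

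**Step 4: larger falls in glucose, insulin fixed.**
- 150 to 120 mg/dL: correct 87/57 − 1 = +52.6%; misapplied 146.5/116.5 − 1 = +25.8%; share kept 0.49.
- 200 to 170 mg/dL: correct 137/107 − 1 = +28.0%; misapplied 196.5/166.5 − 1 = +18.0%; share kept 0.64.

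**Step 5: insulin-driven change.** Insulin multiplies both forms, so a relative change in insulin at fixed glucose gives the same relative change in either. That part is not distorted.

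**The case against.** The strongest reply is that the printed formula is not wrong in itself. It is correct for glucose in mmol/L, HOMA-B carries no mg/dL label, and nothing says that mg/dL values will be entered. A reader might infer that the trial's HOMA-B results will certainly be wrong; the document does not support that. This part of the reply stands, and the point is conditional. What remains is that a primary outcome depends on an unstated conversion, beside a formula that names the other unit. Because a formula is actually printed, this is more than detail left to a fuller document.

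Stronger readings on size also fail.
- One could quote far larger factors, such as 171 at 70 mg/dL, or call the effect halved throughout. The document gives no glucose distribution. At its own cut-points the factors are about 37 and 26, and the loss is smaller still at higher glucose.
- One could try to state a loss of power. That needs standard deviations and correlations for glucose and insulin, which the document lacks. Misapplying the formula compresses noise from glucose as well as signal, so the loss may be large or absent.
- One could suppose that the error would pass unseen. At glucose 150 mg/dL and an illustrative insulin of 10, the index would be 20 × 10/146.5 = 1.4 instead of 360 × 10/87 = 41, which comparison with other HOMA-B results could expose.

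It is also fair to say that the harm is reversible and limited. Glucose and insulin are both measured and are themselves listed as primary outcomes, so the index can be recalculated. The sample size rests on creatinine: "the percentage reduction in creatinine (the primary outcome) is 32.43% in the NS group and 9.84% in the placebo group".

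**Conclusion.** The point holds as a unit mismatch in the definition of a listed primary outcome. If mg/dL values are entered as printed, HOMA-B is about 37 times too small at 120 mg/dL and 26 times too small at 200 mg/dL. A small glucose-driven relative effect loses about 50% at 120 mg/dL and 30% at 200 mg/dL. Because the factor moves with glucose, no constant rescaling of the finished index repairs it, and it does not simply cancel between arms whose glucose differs. If glucose is converted to mmol/L first, there is no error.

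The figures rest on 18 mg/dL per mmol/L and, for the effect sizes, on insulin held fixed. The conclusion does not reach FBS, insulin or HOMA-IR, apart from the missing insulin unit, and it does not touch the sample size or the randomisation.

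**What to change.** In Outcomes measures, do one of the following:
- print HOMA-B as 360 × fasting insulin (µU/mL) / (fasting glucose (mg/dL) − 63); or
- keep the printed formula and state that fasting glucose in mg/dL is divided by 18 before it is used.

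State the insulin unit for both HOMA-IR and HOMA-B, and confirm that the laboratory reports in that unit. If HOMA-B has already been computed, check which glucose unit was entered and, where needed, recalculate it from the stored glucose and insulin values.

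The cost is one line in the protocol and one line of analysis code. No new data are needed. A rule for glucose at or below 63 mg/dL, where the index is undefined or negative, is a separate matter for the analysis plan and is not part of this correction. Dropping such values after randomisation could itself create missing data that differ by arm.

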## Introduction

Diabetes and chronic kidney disease (CKD) are pervasive diseases of the present century, increasing prevalence. Diabetes is the leading cause of renal failure, which ultimately results in the end stage of renal disease (ESRD) and the onset of dialysis or kidney transplantation [1].

By reducing infectious diseases and prolonging the population’s life, CKD has been the most acute chronic non-communicable disease for life-threatening human beings [2]. The prevalence of CKD in different countries depends on many factors, such as gender, age, and economic status. However, it is estimated that 14% of the world’s population is involved in this disease, and accordingly, its prevalence is rising [3]. The prevalence of RRT in many countries, particularly in the Asian continent, is growing, and by 2030, the number of dialysis patients reaches at least 5.4 million [4].

*Nigella sativa* (NS) is an excellent plant from Ranunculaceae and indigenous to Southwest Asia. This plant is used in Iranian traditional medicine to treat various disorders such as respiratory, gastrointestinal, hepatic, and renal disorders. Many of its therapeutic effects have been proven in previous research [5]. Pharmacological studies have shown anti-diabetic, antioxidant, and anti-inflammatory properties of NS because of this plant’s different chemical components. Among these, compounds can be pointed at thymoquinone and nigellidin [6].

About 50% of patients dependent on dialysis are diagnosed with diabetes [7] and are prescribed insulin. Glycosylation of some tissues such as glomerulus and mesangial cells is a determining factor in the progression and development of renal failure. The common indicators for evaluating glycemic status are fasting blood sugar (FBS), glycated hemoglobin (HbA1c), and 2-h postprandial glucose. In previous studies, the positive effect of NS on the reduction of FBS and HbA1c in patients with diabetes mellitus has been well established [8–10].

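### HOMA-B, a listed primary outcome, is printed with mmol/L constants and no unit in a protocol that gives glucose only in mg/dL and states no conversion

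*Protocol article*

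**What the plan says.** Outcomes measures lists the glycaemic primary outcomes as "FBS, HbA1c, GA, serum insulin, insulin resistance and β cell function". The last two are to be computed as HOMA-IR and HOMA-B, and the two formulas are printed side by side:

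- HOMA-IR: "glucose\left(\frac{mg}{dl}\right)\times insulin}{405". Glucose is labelled mg/dL and the divisor is 405.
- HOMA-B: "fasting\ insulin\times 20}{fasting\ glucose-3.5", that is, 20 × insulin divided by (glucose − 3.5). Neither glucose nor insulin carries a unit.

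The only other glucose figures in the article are the strata under Stratified randomization: "FBS < 120 mg/dL, FBS = 120–200 mg/dL and FBS > 200 mg/dL". The article nowhere gives glucose in mmol/L, mentions a conversion, or says which unit goes into HOMA-B.

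**The concern.** Each patient has one FBS value per visit, and it feeds two adjacent formulas. One formula is written for mg/dL. The other carries constants for mmol/L and does not say so. An analyst who follows the text with the only unit it offers would enter mg/dL in both.

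An error by a constant multiplier would do no harm to a test or to a percentage change. This one is not constant. Subtracting 3.5 from a value in the hundreds changes almost nothing, so the index would behave nearly as a rescaled insulin-to-glucose ratio. Lowering glucose is one of the things the trial hopes to show, and the part of any HOMA-B change that comes from it would be understated in a declared primary outcome.

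**Working it through.** The protocol prints no HOMA-B value, so there is no stated figure to reproduce. The check is of the formula and its units.

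**Inputs**
- From Outcomes measures: HOMA-B = 20 × I/(G − 3.5), and HOMA-IR = G (mg/dL) × I/405.
- From Stratified randomization: FBS in mg/dL, with cut-points at 120 and 200 and open ends on both sides.
- Assumed: 18 mg/dL per mmol/L; the usual form of both indices (HOMA-IR divisor 22.5 and HOMA-B constants 20 and 3.5 for glucose in mmol/L); insulin in µU/mL. The article prints none of these.

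**Step 1: which unit the constants belong to.** 405/22.5 = 18, so the HOMA-IR divisor already includes the conversion to mg/dL. The HOMA-B constants do not include it: in mg/dL they would be 20 × 18 = 360 and 3.5 × 18 = 63.

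The size of the offset points the same way. At 120 mg/dL, subtracting 3.5 removes 3.5/120 = 2.9% of the value. In mmol/L the same glucose is 120/18 = 6.67, and subtracting 3.5 removes 3.5/6.67 = 52%.

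**Step 2: the equivalent form in mg/dL.** 20 × I/(G/18 − 3.5) = 360 × I/(G − 63), with G in mg/dL.

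**Step 3: the error if mg/dL is entered as printed.** Correct value divided by literal value = [360/(G − 63)]/[20/(G − 3.5)] = 18(G − 3.5)/(G − 63). Insulin cancels. The two value columns use an illustrative insulin of 10.

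| FBS (mg/dL) | Correct, 3600/(G − 63) | Literal, 200/(G − 3.5) | Factor |
|---|---|---|---|
| 100 | 97.3 | 2.07 | 46.9 |
| 120 | 63.2 | 1.72 | 36.8 |
| 150 | 41.4 | 1.37 | 30.3 |
| 200 | 26.3 | 1.02 | 25.8 |
| 250 | 19.3 | 0.81 | 23.7 |

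Outside these values the factor is 171 at 70 mg/dL, 57.7 at 90 and 21.2 at 400. It grows without limit as FBS approaches 63. Using 18.016 for the conversion instead of 18 gives 36.9 at 120 mg/dL and 25.9 at 200, so the choice does not matter.

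**Step 4: effect on relative change, insulin held constant.**
- FBS 200 to 150: correct (200 − 63)/(150 − 63) = 137/87 = 1.57, or +57%. Literal 196.5/146.5 = 1.34, or +34%.
- FBS 150 to 120: correct 87/57 = 1.53, or +53%. Literal 146.5/116.5 = 1.26, or +26%.

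**Step 5: effect on ranking.** Take one patient with insulin 10 and FBS 100, and another with insulin 20 and FBS 180 (illustrative).
- Correct: 3600/37 = 97.3 against 7200/117 = 61.5.
- Literal: 200/96.5 = 2.07 against 400/176.5 = 2.27.

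The order reverses, so the rank tests named under Statistical analysis would not remove the problem. Nor would adjustment for a baseline value computed in the same way.

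**Step 6: low values.** At FBS of 63 mg/dL or less the correct denominator is zero or negative and the index is undefined. The literal form still returns a positive number there (at 63 the denominator is 59.5), so such cases would pass unnoticed.

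**The case against.** The strongest reply is that the printed HOMA-B formula is correct for glucose in mmol/L. The article writes mg/dL inside HOMA-IR only, and nowhere says that mg/dL values go into HOMA-B. What is demonstrated is therefore a missing unit, and the error occurs only if nobody converts. This stands. A reader might infer that HOMA-B is certain to be wrong; the document does not support that.

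A reader might also quote a fixed range such as 24- to 47-fold. That range corresponds to FBS of about 100 to 240 mg/dL, which the article does not give. The strata are open at both ends, and the factor leaves that range in both directions.

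Nor should the error be read as bias towards one arm. The same formula would apply to both randomized groups at both visits, so it would not by itself create a difference where there is none. It changes scale, ranking and sensitivity.

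The consequence is also limited. HOMA-B is one of 14 measures in the primary list. The sample size is built on another of them: "the percentage reduction in creatinine (the primary outcome) is 32.43% in the NS group and 9.84% in the placebo group". FBS and insulin are measured and reported separately, so HOMA-B can be recomputed at any time.

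Finally, a reader might go on to argue that insulin-treated patients should be left out of the insulin-based indices, because the Introduction says that about half of dialysis patients "are diagnosed with diabetes [7] and are prescribed insulin". That sentence is background on dialysis patients in general. The article does not say how many participants use insulin, and a restriction could remove an unknown share of 46 patients. No such restriction follows from the document.

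What the objection does not remove is that the formula itself is printed here, in a form that fails with the only glucose unit the article provides.

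**Conclusion.** The point holds as a unit mismatch with a conditional consequence. The protocol fixes a listed primary outcome by a formula whose constants suit mmol/L, states no unit, and otherwise works only in mg/dL. If FBS is entered in mg/dL, HOMA-B is too low by 18(G − 3.5)/(G − 63). The relative rise from glucose lowering is understated (roughly half to three-fifths of its true size in the two examples: 26/53 = 0.49 and 34/57 = 0.60), and patients can be misordered. If FBS is converted first, there is no error.

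The sizes rest on the usual form of the index, on 18 mg/dL per mmol/L, and on illustrative glucose and insulin values. Sample size and power are unaffected, as are the measured variables and HOMA-IR.

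**What to change.** In Outcomes measures, do one of the following:

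- print HOMA-B as 360 × insulin (µU/mL)/(FBS in mg/dL − 63); or
- keep 20 and 3.5, and state that FBS is divided by 18 to give mmol/L before it is entered.

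In either case, state the insulin unit for both indices, and state that HOMA-B is not calculable when FBS is 63 mg/dL or less.

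The cost is one formula line and one rule for low values. No new data are needed and no other outcome changes. Any participant with FBS at or below 63 mg/dL at a visit would have no HOMA-B value for that visit. The correction should be made before HOMA-B is computed, and any values already computed from mg/dL should be recalculated.

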### Sample size

The sample size for this trial was calculated based on the primary outcome using the G-power software [23] (procedure of two independent groups) or formula $$ n=\frac{\left({\sigma}_1^2+{\sigma}_2^2\right){\left({Z}_{\frac{\alpha }{2}}+{Z}_{\beta}\right)}^2}{{\left({\mu}_1-{\mu}_2\right)}^2} $$. According to the previous results of NS on renal failure [1], the percentage reduction in creatinine (the primary outcome) is 32.43% in the NS group and 9.84% in the placebo group. By considering an alpha error of 0.05, and the power of 90%, the minimum sample size required for each group is 20 participants, in which with predicting a 15% loss, it will be 23 patients in each group. In total, 46 participants will be recruited in this trial.

### Stratified randomization

The patients will be allocated to either a NS oil or control group by block randomization after stratification based on the frequency of hemodialysis per week (2 or 3 times per week) and the amount of blood sugar (FBS < 120 mg/dL, FBS = 120–200 mg/dL and FBS > 200 mg/dL). This process will be carried out by a statistics specialist using RAS (random allocation software) in block sizes of 4.

### Blinding

The study epidemiologist is responsible for randomization, and the study pharmacist is for blinding the supplements. The supplements, separated by letters A or B, are identical in shape, color, and odor and are placed in similar cans. So, participants, researchers, and data analysts will be blinded after determining interventions.

The blinding code will not be specified until the end of the study except in a medical emergency or a potential study-related adverse event determined by the principal investigator.

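### Two shared letters, A and B, form a single blinding key, so opening the code for one participant can reveal all 46 allocations

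*Protocol article*

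**What the plan says.** The Blinding section of the protocol article makes three statements that have to be read together.

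- Supply coding: "The supplements, separated by letters A or B, are identical in shape, color, and odor and are placed in similar cans".
- Who is to remain blind: "So, participants, researchers, and data analysts will be blinded after determining interventions".
- When the code may be opened before the end of the study: "except in a medical emergency or a potential study-related adverse event determined by the principal investigator".

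The Stratified randomization section adds that allocation is generated "using RAS (random allocation software) in block sizes of 4", within strata formed by dialysis frequency (two levels) and fasting blood sugar ("FBS < 120 mg/dL, FBS = 120–200 mg/dL and FBS > 200 mg/dL").

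Under Interventions, supplements are handed out and patients interviewed every two weeks over 12 weeks. Under Data management, participants have study numbers, but these are described as codes for questionnaires, records and data, not for the supplies.

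**The concern.** A blind that allows emergency code breaks should lose only the participant concerned. A code with one letter per arm cannot do that, because the answer for one can of A is the answer for every can of A and, by elimination, for every can of B. The plan therefore claims a three-way blind and, in the same section, permits an act that can end it for the whole trial. The trigger is not confined to emergencies: an event merely suspected of being related to the study is enough.

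Two things in the plan depend on the blind.

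- **Subjective outcomes.** Under Outcomes measures, HADS and KD-QOL are self-report questionnaires, taken by interview when the patient cannot read, and diet is recorded by the patient over three days.
- **Exclusion.** Under Ethics considerations, participants with acute symptoms attributed to the supplement are excluded, and under Statistical analysis missing data are dropped. An attribution made by someone who knows the arm could change who is analysed.

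**Working it through.** **Inputs**

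| Input | Value | Section |
|---|---|---|
| Participants | 46 (23 per group) | Sample size |
| Supply codes | 2 letters for 2 arms | Blinding |
| Opening of the code mid-study | permitted | Blinding |
| Block size | 4, that is 2 A and 2 B | Stratified randomization |
| Strata | 2 dialysis frequencies × 3 blood-sugar bands = 6 | Stratified randomization |

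**Step 1. The plan's own figure.** The Sample size section starts from 20 per group and allows for 15% loss: 20 × 1.15 = 23 per group, and 2 × 23 = 46. This reproduces "In total, 46 participants will be recruited in this trial".

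**Step 2. What one code break reveals.** Let the key be a rule that assigns the letters {A, B} to {*Nigella sativa*, paraffin}. There are only two such rules. Knowing the treatment behind one letter leaves one rule, so both letters are decoded.

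- Shared letters: 23 + 23 = 46 of 46 allocations are decoded for a person who also knows the letters.
- Participant-specific codes: 1 of 46 (2.2%) is decoded per break.

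If p is the chance that a given participant's code is opened, and breaks are independent, the chance that the trial-wide key is opened at least once is 1 − (1 − p)^46. The article gives no p, so no probability is put on this. The result is conditional on a break.

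**Step 3. Which outcomes are exposed.** Under Outcomes measures, the primary outcomes are blood measurements, indices computed from them, and urine volume. HADS, KD-QOL and dietary intake are secondary. Knowledge of the arm can move the second group directly. It reaches the first group mainly through exclusions.

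**Step 4. Secondary: prediction of the next letter.** There are six equally likely orderings of AABB. For an observer who knows the block size and all earlier letters in the stratum:

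| Position in block | Letter certain | Best guess correct |
|---|---|---|
| 1 | 0 | 1/2 |
| 2 | 0 | 2/3 |
| 3 | 1/3 | 1/3 × 1 + 2/3 × 1/2 = 2/3 |
| 4 | 1 | 1 |

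The averages are (1/3 + 1)/4 = 33.3% certain and (1/2 + 2/3 + 2/3 + 1)/4 = 70.8% guessed correctly, against 50% under simple randomisation. These hold for complete blocks.

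With 46 patients spread over six strata, some blocks stay incomplete. Simulation (20,000 runs for each of three assumed distributions over the strata) gives 12.8 to 13.0 letters certain, or 28%, and about 31.5 of 46 guessed correctly, or 68%. The result hardly depends on the assumed distribution.

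Mixing blocks of 4 and 6 at random (illustrative, 3,000 runs for each of two assumed distributions) lowers the certain letters to about 2.4 to 2.7 of 46, or 5 to 6%. The best-guess rate falls only to about 67%.

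All of these percentages concern letters. Without the key, a predicted letter does not say which treatment comes next.

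**The case against.** The strongest reply is that the article does not say the letter is the only mark on a can, or that recruiters and interviewers see it. Labelling details and the mechanics of emergency unblinding are commonly left to a full protocol. That is fair as to what is left out. But the article states the letter coding positively and rests its blinding claim on it. An added participant number would not help while the letter can also be seen. If the letters are in fact used only by the pharmacist and never leave the pharmacy, the point falls away.

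It can also be said that opening the key does not by itself inform everyone. It informs the person who opens it, and others only if it spreads. The analyst receives a cleaned dataset at the end. This stands, and it is why the conclusion is limited to people who have both the key and the letters. The harm also needs a code break, and the Interventions section expects only rare and mild effects.

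A reader might infer more: that fixed blocks of 4 defeat concealment of the next treatment, that patients compare letters in one dialysis unit, or that publication gave recruiters the block size. The documents do not support these.

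- Before the key is opened, a predicted letter carries no treatment information.
- The article names one hospital and says nothing about patients comparing cans, and comparing letters would not reveal the treatment without the key.
- Under Trial status, sampling was almost finished when the article was written, with completion expected by 20 August 2020, so publication could have told recruiters little in time.

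**Conclusion.** The point holds as a weakness of the described blinding method. As written, one permitted code break decodes 46 of 46 allocations, instead of 1 of 46, for anyone who has both the key and the letters. This rests on two assumptions: that the letters are visible on the supplies or in the records outside the pharmacy, and that a code is opened at least once while outcomes are still being collected or analysed.

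The consequence is moderate. The subjective secondary outcomes and the exclusion judgement are exposed. The mostly laboratory primary outcomes are much less so. The change is a cheap improvement and not a condition for the trial to be valid.

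Block predictability is secondary. About 28% of letters would be certain to someone who knows the block size and tracks letters by stratum, and this matters only once the key is known. It then adds to the main problem, because a predicted letter becomes a predicted treatment for any patient still to be enrolled.

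**What to change.** 1. The pharmacist labels each can with a participant-specific number taken from the randomisation list, with no A or B on the can.
2. The pharmacist holds one emergency code per participant, so that a break reveals that participant only. The circumstances in which a code may be opened are not altered by this proposal.
3. The analyst receives newly coded arm labels, unrelated to any letter used during the trial. This remains possible until the analysis starts.
4. The Blinding section is reworded to describe these steps.

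For participants already on treatment, relabelling can be done at the next two-weekly supply for as long as dispensing continues. The cost is a small burden on the existing pharmacist for at most 46 participants, plus a check of each new label against the list, because relabelling during the trial carries a risk of error. Letters already seen cannot be erased, so the protection is partial for anyone supplied before the change. Dose, outcomes and sample size are unaffected.

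Varying the block size is optional. With enrolment almost finished it would affect few participants, and it barely lowers the best-guess rate (about 68% to about 67%), although it does reduce the letters known with certainty (28% to about 5 to 6%).
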